## Abstract

**Background:**

Psychotic disorders often develop a chronic course with devastating consequences for individuals, families, and societies. Early intervention programs for people in the first 5 years after the initial psychotic episode (early psychosis) can significantly improve the outcome and are therefore strongly recommended in national and international guidelines. However, most early intervention programs still focus on improving symptoms and relapse prevention, rather than targeting educational and vocational recovery. The aim of the present study is to explore the effects of Supported Employment and Education (SEE) following the Individual Placement and Support (IPS) model in people with early psychosis.

**Methods:**

The SEEearly trial compares treatment as usual (TAU) plus SEE to TAU alone in outpatient psychiatric settings. The study is a six-site, two-arm, single-blinded, superiority randomized controlled trial (RCT). Participants are randomly assigned (1:1) to the intervention or control group. Aiming to recruit 184 participants, with an assumed drop-out rate of 22%, we will be able to detect a 24% difference in the main outcome of employment/education with 90% power. We make assessments at baseline and at 6- and 12-month follow-ups. Outcome data on employment/education, medication, and current psychiatric treatment is obtained monthly through phone based short assessments. The primary outcome is steady participation for at least 50% of the 12-month follow-up in competitive employment and/or mainstream education. Secondary employment outcomes capture length of employment/education, time to first employment/education, monthly wages/educational attainment, and social return on investment (SROI). Secondary non-employment outcomes include subjective quality of life, psychopathology, substance use, relapse, hospitalization, and functional impairment. To be eligible, participants must be between 16 and 35 years, fulfill diagnostic criteria for early psychosis, and be interested in competitive employment and/or mainstream education.

**Discussion:**

In SEEearly, we hypothesize that participants with psychosis, who receive TAU plus SEE, present with better primary and secondary outcomes than participants, who receive TAU alone. Positive results of this study will justify SEE as an evidence-based strategy for clinical routine treatment in people with early psychosis.

**Trial registration:**

SEEearly was registered nationally and internationally in the German Clinical Trials Register (DRKS; identifier: DRKS00029660) on October 14, 2022.

## Administrative information

Note: the numbers in curly brackets in this protocol refer to SPIRIT checklist item numbers. The order of the items has been modified to group similar items (see http://www.equator-network.org/reporting-guidelines/spirit-2013-statement-defining-standard-protocol-items-for-clinical-trials/).

## Introduction

### Background and rationale {6a}

Psychotic disorders often lead to a chronic course with devastating consequences for individuals, families, and societies, usually with first onset during adolescence or early adulthood [1, 2] when individuals are typically pursuing their education, employment, and career trajectories. The low rates of completing secondary education and obtaining competitive employment with education, additionally to vocational recovery rates of only 13.5% [3] represent one of the main burdens in individuals and their families and account for the majority of costs the illness causes for societies [4, 5].

Early intervention programs, which provide intensive, phase specific, psychosocial, and pharmacological treatment for people in the first 5 years after the initial psychotic episode (a phase referred to as *early psychosis* [6]), can significantly improve the outcome and reduce negative consequences of early psychosis [7–9]. Because of these findings, national and international guidelines support the implementation of early intervention programs with a high level of recommendation [10–12]. However, to date, most early intervention programs for people with early psychosis still focus on improving symptoms and preventing relapse, rather than targeting educational and vocational recovery [7, 8, 13]. This is inappropriate because engagement in work and education has a high priority for young people with early psychosis and significantly reduces the social disability associated with the disorder [14, 15].

In the present trial, we investigate the effects of Supported Employment (SE) following the IPS model, which focuses on obtaining competitive work through improvement of functioning and vocational recovery in people with early psychosis [16, 17]. Furthermore, since many adolescents or young adults with early psychosis are still in secondary education, the IPS model is extended to achieve mainstream education: Supported Employment and Education – SEE [18]. There is strong evidence, that SE in adults with severe mental illness (SMI) leads to much higher rates of competitive job acquisition, increased working hours per week, and higher wages compared to general rehabilitation services [19–21]. Secondary education, SE, and competitive employment correlate positively with clinical, social, and economical outcomes as well as with quality of life [22–24]. Competitive employment is defined as jobs that anyone can apply for regardless of disability status. Mainstream education is defined in accordance with the Organization for Economic Cooperation and Development (OECD) [25] as educational programs leading to a qualifying degree and open to the general public. In Germany, this includes the following educational settings: secondary education (“sekundärer Bildungsbereich”), education examinations, internships (e.g., “Praktisches Jahr”), apprenticeship that generally lasts for 2 to 3 years and enable people to carry out a professional activity (“Berufsausbildung”), and higher education (university, university of applied sciences). Vocational education programs in line with traditional vocational rehabilitation (TVR) approaches following the “first train – then place” approach do not account as mainstream education [18].

Despite the proven effectiveness and recommendation in national and international guidelines [11, 12], there are only six RCTs of SEE in early psychosis available up to now [16, 20, 21, 26–28]. These include mostly young adults above 18 years, mainly focus on employment and not on both employment and education, sample sizes are limited in several of them, and none of the studies is a multi-site study. SEEearly therefore is the first multisite RCT of SEE in adolescents and young adults with early psychosis worldwide. SEEearly overcomes the limitations of the RCTs mentioned above. In particular, this involves (a) applying SEE rather than SE and (b) considering the primary outcome “steady participation for at least 50% of the 12-month follow-up period in competitive employment and/or mainstream education” rather than “at least one day”, (c) a sample size that is large enough to determine the relative effects of TAU plus SEE in comparison to TAU, (d) applying a meaningful intervention and follow-up time period, (e) using a standardized manual of SEE, (f) measuring the fidelity of the intervention by applying the IPS Fidelity Scale for Young Adults [18], and (g) applying an economical evaluation.

### Objectives {7}

The central hypothesis of SEEearly is that participants with early psychosis who receive TAU plus SEE show better competitive employment and/or mainstream education outcomes than participants who receive TAU alone. This article describes the protocol for the SEEearly trial.

### Trial design {8}

The SEEearly study is a six-site, prospective, rater blinded, two-arm, superiority RCT. After being assessed for eligibility, fulfilling inclusion but not exclusion criteria, and providing written informed consent, participants are randomized with a 1:1 ratio to either TAU plus SEE or to TAU alone.

The primary outcome and secondary employment outcomes, current medication, and current psychiatric treatment are assessed monthly. Assessments regarding further secondary outcomes are made at baseline and at 6 and 12 months of follow-up (see Fig. 1 and Table 1).

**Fig. 1 Fig1:**
[figure not shown]
Trial timeline and design

**Table 1 Tab1:** Content and timeline of participant ratings

**Content of ratings**	**Baseline/t0**						**t1**						**t2**
**/month**	**Baseline**	**1**	**2**	**3**	**4**	**5**	**6**	**7**	**8**	**9**	**10**	**11**	**12**
**By rater**													
Diagnosis acc. to DSM-5 and ICD-10, sociodemographic background, living situation, expectations reg. employment/education	x												
Prior psychiatric treatment	x												
Ongoing psychiatric treatment	x	x	x	x	x	x	x	x	x	x	x	x	x
Ongoing medication	x	x	x	x	x	x	x	x	x	x	x	x	x
Primary outcome		x	x	x	x	x	x	x	x	x	x	x	x
Secondary outcome (employment and education)		x	x	x	x	x	x	x	x	x	x	x	x
Psychopathology (PANSS)	x						x						x
Functional impairment (Mini ICF-APP, GAF)	x						x						x
Social support	x						x						x
Substance use (ASI, DFAQ-CU)	x						x						x
Social return on investment													x
**Self-rating**													
Subjective quality of life (WHOQOL-BREF)	x						x						x
Motivation for Change Questionnaire (CQ)	x						x						x
**Only intervention group (SEE)**													
Efficacy belief (JSSE-O)			x										
Work alliance (WAI-VR)			x										x
Documentation of the SEE-specialists		x	x	x	x	x	x	x	x	x	x	x	x

## Methods: participants, interventions, and outcomes

### Study setting {9}

The recruiting period started in October 2022 and will end on December 31, 2023. Participants are recruited from outpatient units across the six involved sites:

### Eligibility criteria {10}

Inclusion criteria are [1] adolescents and young adults aged between 16 and 35 years with [2] a clinical diagnosis of early psychosis. The latter is being defined in accordance with the largest trial of early intervention in psychosis worldwide so far (*n* = 404; [6]): SEEearly participating patients have to fulfill the DSM-5 (Diagnostic and Statistical Manual of Mental Disorders, volume 5) schizophrenia spectrum criteria or other psychotic disorder criteria. In addition, the onset of the first episode of psychosis should not be longer than 5 years ago or initial presentation to mental health services due to psychotic symptoms was within the last 5 years. Structured Clinical Interview for DSM-5 (SCID), Modules B and C, is used to confirm diagnoses according to the DSM-5. Further inclusion criteria are [3] general interest in competitive employment and/or mainstream education and [4] sufficient German language abilities (≥ A2). Exclusion criteria are [1] learning disability or mental retardation, [2] insufficient German language abilities (< A2), and [3] physical or organic handicap that seriously impedes work or educational functioning.

### Who will take informed consent? {26a}

Recruitment is taking place in the outpatient units of the involved sites. Clinicians and/or psychologists refer patients interested in participating in the study to a research assistant (psychologist) who, in turn, schedules an appointment. The research assistant assesses the patients for eligibility, provides written and verbal information about the research project, and answers existing questions before signing the informed consent. Underage participants need the consent of a parent or guardian (Participant Information Sheet for Adults, Adolescents, Custodian and Participant Consent Form in German are available from the corresponding author on request).

### Additional consent provisions for collection and use of participant data and biological specimens {26b}

N/A. There are no additional consent provisions as participant data will only be used for the purpose of the SEEearly trial. Biological specimens are not collected.

## Interventions

### Explanation for the choice of comparators {6b}

In SEEearly, we compare TAU plus SEE (intervention) to TAU alone (control condition) in the respective recruitment centers for 12 months. TAU is defined as common multidisciplinary clinical practice for adolescents and young adults with early psychosis. This includes medical review, pharmacological treatment, psychosocial support including social work counseling, and referral to external government-funded vocational programs. Type and frequency of the psychosocial support interventions in the control condition is being documented. Pharmacological treatment is continuously assessed and the respective chlorpromazine equivalents are calculated. To standardize support regarding work and education across study sites and to make sure that employment and education is being addressed with participants of the TAU condition as well, all social workers involved with participants in the TAU condition are obligated to have at least one consultation with the participants regarding competitive employment and/or mainstream education. Participants of the TAU condition do not have access to SEE treatment during the time of the trial but will be offered IPS after completing the study, if available at the respective mental health service.

### Intervention description {11a}

SEE is based on the nine IPS principles (SE and SEd [Supported Education]). IPS is an evidence-based practice for helping people with severe mental illness to gain and maintain competitive employment and/or mainstream education [16–18, 29]. SEE is delivered by SEE-specialists trained according to a standardized SEE manual [18], which has been translated into German in the preparation phase of the project. Every participant is being assigned to a SEE-specialist, who provides services based on the IPS principles. These include that (a) the SEE-specialist builds partnerships with employees and education program staff and provide follow-up support to both the employee and the employer once work is obtained and (b) the SEE-specialist is part of the mental health treatment team and is therefore located in the same office space and also attends and participates in client’s treatment teams using a shared case management and documentation system.

For the present trial, interventions take place for a duration of 12 months for each participant in the intervention group and range from engagement techniques (e.g., motivational interviewing) to individualized competitive employment and/or mainstream education searches and from experience-based assessment to benefits in counseling/work incentives planning. In cases where participants are hard to reach, SEE-specialists perform repeated attempts to establish contact and document used strategies and the outcome. If contact is not successful over a period of 3 months, the follow-up will stop.

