### Plans to promote participant retention and complete follow-up {18b}

In cases where participants are hard to reach for follow-up, the research assistant performs repeated attempts to establish contact and document used strategies and the outcome. If contact is not successful over a period of three months, the follow-up will stop.

In the event of premature withdrawal from the trial, previously collected data will be included in the evaluation if the participant does not object this procedure.

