## Statistical methods

### Statistical methods for primary and secondary outcomes {20a}

#### Primary outcome

Confirmatory analysis will be conducted based on the intention-to-treat (ITT) principle. The primary efficacy aim is to show that the percentage of participants who participate steadily over at least 50% of the 12-month follow-up in competitive employment and/or mainstream education is higher in the intervention group than in the control group. A logistic regression model adjusted for study site will be applied with a 95% confidence interval for group comparison. The two-sided significance level is 0.05.

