### Methods in analysis to handle protocol non-adherence and any statistical methods to handle missing data {20c}

Efforts are made to follow-up participants who dropped out from treatment in order to collect outcome data to reduce missing and to detect underlying structures about missing data mechanisms (e.g., missing at random, MAR). Missing values will be imputed using multiple imputation chained equations (MICE; [56]).

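### The 3-month no-contact rule can be read as ending outcome follow-up in the SEE arm alone when SEE contact is lost, and the shared version stops outcome collection for good although month-6 and month-12 assessments are scheduled

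*Protocol article*

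**What the plan says.** All references are to the protocol article.

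- **Intervention description {11a}.** On hard-to-reach participants: "In cases where participants are hard to reach, SEE-specialists perform repeated attempts to establish contact and document used strategies and the outcome". The next sentence is "If contact is not successful over a period of 3 months, the follow-up will stop". SEE-specialists serve only the intervention arm. The same section also uses follow-up for part of the intervention: "provide follow-up support to both the employee and the employer once work is obtained".
- **Retention section {18b}.** Here the task falls to a different role: "In cases where participants are hard to reach for follow-up, the research assistant performs repeated attempts to establish contact". The rule that comes after it reads "If contact is not successful over a period of three months, the follow-up will stop". This rule covers both arms and plainly concerns outcome data.
- **Missing data {20c}.** "Efforts are made to follow-up participants who dropped out from treatment in order to collect outcome data to reduce missing". Missing values are then imputed by chained equations.
- **Statistical methods, Primary outcome {20a}.** "Confirmatory analysis will be conducted based on the intention-to-treat (ITT) principle".
- **Outcomes {12}, Table 1 and {18a}.** The primary outcome is taking part in work or education for at least half of a 12-month period. It is recorded monthly by research assistants, with fuller assessments at months 6 and 12.

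**The concern.** The closing sentences of the {11a} and {18b} rules are almost identical, but they hang on different people's contact. If *the follow-up* means the same thing in both, a SEE participant can leave outcome follow-up by either of two routes, failed research-assistant contact or failed SEE-specialist contact. A control participant has only the first. The extra route is disengagement from the intervention, which is the situation in which {20c} says outcome data will still be sought. An ITT comparison needs outcomes collected regardless of adherence and in the same way in both arms.

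The {18b} rule raises a different issue. It is the same in both arms, but it is final. As written, someone unreachable for three months early in the year is not approached again, although one contact at month 6 or month 12 could establish what happened in the missed months.

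The article expects 22% drop-out, about 40 of 184 participants (184 × 0.22 = 40.5). Avoidable loss of the primary outcome therefore matters, and data not collected while follow-up runs cannot be restored at analysis.

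**Working it through.** **1. The two readings of {11a}.**

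| Reading of *the follow-up* in {11a} | Stopping triggers, SEE / control | Fits {20c}? | Fits ITT? |
|---|---|---|---|
| SEE-specialist's own contact attempts | 1 / 1 (the {18b} rule only) | yes | yes |
| Outcome follow-up | 2 / 1 | no | poorly |

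For the first reading: the sentence sits in the intervention section, which also speaks of follow-up support. For the second: sections {12} and {20a} use follow-up for the 12-month outcome period, and {18b} repeats the sentence in that sense. The text does not decide between them.

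**2. The plan's own figures.** Inputs from Sample size {14}: 40% vs 16%, two-sided 0.05, power 0.90. With a mean rate of 0.28,

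n per arm = [1.960 × √(2 × 0.28 × 0.72) + 1.282 × √(0.40 × 0.60 + 0.16 × 0.84)]² / 0.24² = 71.5, so 72.

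Power at 72 per arm is 0.902. Drop-out: 144 / 0.78 = 184.6, against 184 stated, an immaterial difference. The sample size reproduces; this point reveals no numerical error.

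**3. Arm-specific loss by hand.** The article gives no loss by arm, so everything here is assumed: 92 randomised per arm, 22% uninformative loss in both, and a further fraction x of the SEE arm lost through the literal {11a} rule, with success rate q among those lost. Among completers the SEE rate shifts by

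x × (0.40 − q) / (0.78 − x).

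| x | Power at true 40% vs 16% | Shift if q = 0 | Shift if q = 0.16 | Shift if q = 0.40 |
|---|---|---|---|---|
| 0 | 0.901 | 0 | 0 | 0 |
| 0.05 | 0.892 | +2.7 points | +1.6 | 0 |
| 0.10 | 0.881 | +5.9 | +3.5 | 0 |
| 0.15 | 0.869 | +9.5 | +5.7 | 0 |

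The power cost is small. The q = 0 column is an extreme in which every extra lost participant is a failure. The shift turns negative if q exceeds 0.40, for example if people leave SEE contact because they have found work.

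**4. Month-by-month simulation.** Assumptions: 400,000 per arm; nobody engaged at the start; monthly start probability 0.082 (SEE) and 0.029 (control); 97% monthly retention once engaged. This gives success rates of about 40% and 16%. Assumed monthly loss is 3% when not engaged and 0.5% when engaged.

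- *Same rule in both arms:* 21% (SEE) and 25% (control) are lost. Completers 44.4% vs 18.8%, difference 25.6 points against a true 23.9.
- *SEE loss when not engaged raised to 4.5% a month:* 29% of SEE are lost. Completers 47.2% vs 18.7%, difference 28.5 points, so 28.5 − 23.9 = 4.6 too large.

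Completers are only a sensitivity population ({20b}). With the higher SEE loss, and months imputed within arm from each person's recorded status, the differences in points are:

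| What loss depends on | True | Completers | Imputed |
|---|---|---|---|
| Status in the month just reported | 23.6 | 28.4 | 23.5 |
| Status in the previous month | 23.8 | 28.4 | 23.8 |
| Status in the current, unobserved month | 23.9 | 28.7 | 24.9 |

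The simulation error of a true difference is about √(0.3744 / 400,000) = 0.1 point. Bias is therefore 4.6 to 4.8 points in completers, and about 0 to 1 point after month-level imputation.

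**The case against.** The strongest reply is that {11a} and {18b} divide the work: {11a} limits SEE outreach and {18b} limits outcome assessment. Research assistants collect outcomes separately from SEE-specialists and are to stay blind ({17a}, {17b}). If lost SEE contact ended their assessments, the stop itself would point to the participant's arm. That makes the benign reading at least as likely as the other. It does not settle the wording, which six sites have to apply.

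A reader might infer three stronger claims that the article does not support.

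- *That outcome data are being lost unequally by arm.* No loss by arm is reported, and extra SEE contact might improve retention.
- *That {18b} contradicts {20c} or ITT.* It does not. Failing to answer the research assistant is not treatment drop-out, making efforts is compatible with a limit on them, and the limit is the same in both arms.
- *That the primary result would be inflated by some 4.5 points.* That is a completer figure. The planned imputation removes most or all of it if it works from the monthly records. The article does not say whether it does, but that detail commonly belongs to the analysis plan.

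It is also fair to say that a symmetric three-month limit is a legitimate choice, and that recall over many months is weaker than prospective monthly data. Both stand. But a recalled month is usually worth more than none, and the later assessments are scheduled anyway.

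**Conclusion.** The concern holds in a limited form. The {11a} sentence is ambiguous. On one of its two readings it creates a stopping rule in the SEE arm only, which conflicts with the commitment in {20c} and sits badly with ITT. Separately, {18b} ends outcome collection permanently in both arms when scheduled assessments could recover missed months.

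The consequence is avoidable loss of primary-outcome data, and loss that differs by arm if {11a} is followed literally. Size and direction of bias are unknown. With the assumed monthly loss rates it is about 0 to 1 point if imputation uses monthly history, about 4.5 to 5 points in completers, and zero if the loss is unrelated to outcome. The case for acting rests on the conflicting text and the low cost of repair, not on a demonstrated bias.

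**What to change.** Reconcile {11a}, {18b} and {20c}:

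1. In {11a}, say what stops after three months, and state that lost contact with the SEE-specialist does not end outcome assessment.
2. In {18b}, let the monthly calls pause after three months without contact, but attempt the month-6 and month-12 assessments for every randomised participant who has not withdrawn consent, asking month by month about work and education in the missed period.
3. Let {20c} refer to this rule.

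The cost is a wording amendment and a few extra attempts by existing research assistants, for at most about 40 participants at the assumed drop-out. The downside is longer recall for the recovered months. The change concerns outcome data collection only, not how SEE contact is managed.
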